**Fig. 4 Fig4:**
[figure not shown]
Model reflecting the training program implemented with coaches to deliver the HIV preventive intervention

Coaches also receive 1 month of training that covers IRB certification and human subject training, as well as how to report all conversations, contacts, and their content daily on the mobile phone system. Coaches attend a weekly supervision meeting to review progress, and reinforce key skills and content. In-service training occurs routinely on a monthly basis.

#### Process measures for soccer

Using a mobile phone survey programmed by Mobenzi at each practice or game, coaches report on: attendance, whether HIV, alcohol and drug RDT are administered, the content area discussed during the coaching meeting (e.g., alcohol use, sexual relationships), and the skills used by the coach. Stellenbosch supervisors randomly visit either practices or games once every 2 weeks to provide on-site supervision and monitoring. HIV testing is offered at the soccer field by a mobile testing van and uptake is documented (but not the test results). RDT for alcohol, marijuana, methamphetamine, and mandrax are administered randomly once per week to all participants.

#### Condition 3: soccer league and vocational training (SL-V)

For the first 6 months of intervention delivery, all procedures described above for the SL condition are replicated for all young men in eight neighborhoods (*n* = 400 men). The selection, training, and monitoring system for coaches and participants is the same in both conditions for the first 6 months, with soccer offered 2 days per week and a game on Saturdays.

After 6 months, all young men are offered vocational training through either Silulo Ulutho Technologies or Zenzele Training and Development programs. In these programs, participants have access to accredited training programs in public computer courses, woodwork, and welding. Both programs are located in Khayelitsha, which is close to participants’ homes, thus avoiding transport-related barriers. Additionally, the training programs occur in a mentor-mentee context so that participants can develop the interpersonal skills required for employment.

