### Data monitoring

We formed an independent Data Safety Monitoring Board, comprised of four consultants with substantial research experience in South Africa and the United States. The DSMB meets twice annually and reviews interim analyses after each round of follow-up data collection at 6, 12, and 24 months. Stopping the trial will occur only if there appears to be iatrogenic effects associated with men meeting in groups and exacerbating each other’s risk acts. In particular, we monitor criminal acts, sexual risk, and increased substance use that could be associated with the intervention at the 6- and 12-month interim analyses.

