### Assessments

At the local storefront assessment center, trained interviewers obtain written voluntary informed consent and then administer a 1-h assessment, recording responses on mobile phones using a program designed by Mobenzi Technologies. Participants receive about ZAR 150 for their time to complete the interview (incentives are adjusted over time for inflation). Assessment data are coded with personal identification numbers (PIDs) and do not include any personally identifiable information. De-identified assessment data are available through a password-protected, cloud-based database and accessed by UCLA and Stellenbosch University for quality control and later analyses. Assessments are conducted at the baseline recruitment and at 6, 12, and 24 months later. Interviewers report all adverse events to their supervisors in real time and identify these as study-related (or not). Serious adverse events (death, criminal acts) are reported to all Investigators, Institutional Review Boards, and funding agencies within 48 h.

At the time of enrollment, interviewers collect detailed locator information from participants, including the names and addresses of friends and family members and favorite hangout spots, locally and in the Eastern Cape, where the ancestral homes of many Cape Town residents are located. The Assessment Team, led by Stellenbosch University, is experienced in using this information to retain participants, consistently maintaining participant retention rates at or above 85% [48].

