#### Condition 2: soccer league (SL)

All young men in eight neighborhoods (*n* = 400) receive soccer training for 1 year. After all of the baseline assessments are completed in a specific neighborhood, soccer coaches visit each participant individually to describe the intervention in detail, invite them to the soccer league, and answer any questions. The league includes at least two and usually three teams per neighborhood (14 men minimum per team needed, anticipating some absenteeism), resulting in approximately up to 24 teams in this condition. Each week, there are 2 days of practice and 1 day for a game with another team. Teams are led by coaches who are recruited from the broader township (versus target neighborhoods) to safeguard players’ confidentiality (coming from the same neighborhood is likely to inhibit men’s disclosures about problem issues, fearing the coach may tell others). Coaches cannot be regulars at the local shebeens or known drug addicts, and must have held a job at some time previously, have experience playing soccer, and demonstrate good social skills. In this way, coaches are positive peer deviants (i.e., role models) for participants [53, 54]. About 30% of persons applying to be coaches are hired, based on initial interviews and observations completed during the coach training.

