### Data analysis

Histograms for continuous variables (CES-D, AUDIT-C) will be plotted and screened for outliers and incorrect data and we will build tables for categorical variables, marginally and by treatment condition. Longitudinal data analyses follow the general analysis plan described in detail in Weiss [63]. Longitudinal data will be plotted for continuous variables and empirical summary plots (means ± 2 SE over time, by treatment condition with means and SEs calculated simply at each time point within condition) for all variables.

Neighborhoods and soccer teams are nested within condition; we will use hierarchical regression models with random effects for neighborhood, team within neighborhood, and young men. However, for many outcomes, one or other of the random effects variances will likely be small. Traditional maximum likelihood (ML) software has trouble fitting random effects models when random effect variances are modest or small. However, it is important to include these random effects in the model and to have non-zero variance estimates to properly assess the evidence in the data about the conditions, no matter the size of the variances. Working with SAS or Stata and having to specially adapt models to every outcome due to ML neighborhood and team variance estimated as zero is expensive. The simple but flawed solution of setting the variances to zero causes *p* values comparing conditions to be inappropriately smaller than they merit. In contrast to ML methods, Bayesian methods will not set variance estimates equal to zero, and will properly fit the models we need to our data. We will use the software MCMCglmm [64] or JAGS in R [65], as they both can fit the needed generalized linear mixed models (GLMMs) for discrete and continuous outcomes, estimate all variances appropriately, and run without producing errors, thus saving substantial time and improving the accuracy of the resulting conclusions. To calculate the two degrees of freedom chi-square statistic, we will calculate the posterior mean and covariance matrix of the difference of differences SL-V minus CC, and SL minus CC at 24 months minus baseline and calculate a two degrees of freedom chi square statistic for which we calculate a tail area. The 24-month outcome will be the main time point, with secondary calculations for 6 months minus baseline and 12 months minus baseline.

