### Missing data

We will analyze: 1) missing data longitudinally as a binary outcome at 6, 12, and 24 months, omitting the first time point; 2) separately, we will analyze which men drop out as a single binary outcome. Baseline sociodemographic variables (e.g., age, education) will be examined as predictors in each analysis; and 3) we will use intervention conditions as predictors of baseline sociodemographics. Any significant variables (analyses 1 and 2) and any sociodemographics that are predicted by condition (analysis 3) will be collected together and used as additional predictors in sensitivity analyses when assessing significance of the conditions.

Additional information is available as counts for several outcomes (e.g., number of days of drug use, number of partners) and continuous variables (CES-D, AUDIT) which we will analyze in secondary analyses. Among the subset of HIV-positive participants, we will analyze the HIV treatment continuum variables (i.e., linkage and retention in care, uptake and adherence to ARV). For binary outcomes measured at baseline and 6, 12, and 24 months, we expect to treat time categorically, and model main effects for condition, time, and time by condition interaction. Primary interest is the differences among conditions in the change from baseline to 12 months and to 24 months, and secondarily the change to 6 months. Assuming significant differences between conditions in changes from baseline, we will estimate pairwise differences (SL-V minus SL; SL minus CC; SL-V minus CC) in changes from baseline to months 6, 12, and 24.

Finally, we will summarize the frequency of practice elements delivered by coaches from process monitoring data in tables overall and by coach. We wish to see if supervisor ratings are predictive of practice element data that we collect; the model is longitudinal repeated measures but with coaches as the subject. Also, using GLMMs, we will analyze the process measures that are measured regularly (daily/weekly/monthly) during the soccer intervention to compare SL and SL-V conditions and to see how they relate to future employment. We expect that coaches who most frequently use goal setting and problem solving will have the young men with the greatest improvements. One year after the completion of data collection, a data set stripped of potential identifiers will be provided to the National Institutes of Health and available at UCLA.

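### The 6-month analysis keeps SL and SL-V as separate treatments although both have delivered the same program by then; the test is valid but loses power, and SL-V minus SL at month 6 cannot show a vocational-training effect

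*Protocol article*

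**What the plan says.** **What is delivered.** Under Condition 3 (SL-V), for the first 6 months of delivery "all procedures described above for the SL condition are replicated for all young men in eight neighborhoods", and "The selection, training, and monitoring system for coaches and participants is the same in both conditions for the first 6 months". The component that separates the arms comes later: "After 6 months, all young men are offered vocational training through either Silulo Ulutho Technologies or Zenzele Training and Development programs".

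**When the visit falls.** Under Assessments: "Assessments are conducted at the baseline recruitment and at 6, 12, and 24 months later". Under Condition 2 (SL), soccer begins only once a neighborhood's baseline interviews are finished: "After all of the baseline assessments are completed in a specific neighborhood, soccer coaches visit each participant individually to describe the intervention in detail".

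**How month 6 is analyzed.** Data analysis defines, for each outcome, a 2-df chi-square on the changes from baseline in SL-V minus CC and SL minus CC. Its main time point is 24 months, "with secondary calculations for 6 months minus baseline and 12 months minus baseline". The section headed Missing data adds that, given significant differences between conditions, "we will estimate pairwise differences (SL-V minus SL; SL minus CC; SL-V minus CC) in changes from baseline to months 6, 12, and 24". It also places the change to 6 months second to the changes to 12 and 24 months.

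**Monitoring.** Data monitoring says: "Stopping the trial will occur only if there appears to be iatrogenic effects associated with men meeting in groups". It names the 6- and 12-month interim analyses but no statistical test.

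Nowhere does the article pool the soccer arms at 6 months, or say that no SL-V versus SL difference is expected then.

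**The concern.** The analysis uses one three-arm framework at every visit, but the design has only two delivered treatments at the first follow-up. Two things follow.

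- **Efficiency.** The only intervention question that month 6 can answer is whether soccer differs from control. The 2-df test spends its second degree of freedom on a difference between two arms that have received the same program. Each pairwise contrast with control uses only half of the soccer data.
- **Interpretation.** SL-V minus SL at month 6 is listed beside the 12- and 24-month versions of the same contrast, as if it measured the same thing. Before vocational training is offered it cannot estimate that training's effect. A chance difference could be read as a difference between programs.

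At stake is the sharpness and clarity of a secondary analysis, not the primary conclusion.

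**Working it through.** **1. Timing.** The 6-month visit is counted from baseline recruitment. Soccer starts after all baseline assessments in the neighborhood. So 6 months from baseline is at or before 6 months of delivery, and vocational training is offered only after 6 months of delivery. A visit held on schedule therefore precedes it.

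**2. Inputs** (sample-size paragraph at the end of the section headed Missing data, unless noted): 400 men per condition; 20% loss; design effect 1.49 × 1.16 = 1.7284; alpha 0.05, two-sided (Outcome measures); detectable pairs 30% vs 17%, 30% vs 41% and 40% vs 26%; pilot loss of 5% at 6 months.

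**3. The plan's own figure.** The article gives no power for the 6-month analysis. For the stated size, the two-proportion formula multiplied by 1.7284 / 0.8 gives, per condition:

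- 30% vs 17%: 166 → 359, or 181 → 391 with continuity correction. The stated 400 is reproduced with the correction.
- 40% vs 26%: 176 → 380, or 410 with the correction. This is also close to 400.
- 30% vs 41%: 296 → 640, or 314 → 678 with the correction. This does not reproduce 400. It is a separate matter on which this point does not rest.

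**4. Effective size per arm.** 400 × 0.80 / 1.7284 = 185 with 20% loss; 400 × 0.95 / 1.7284 = 220 with 5% loss.

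**5. Power at month 6 with the same effect in both soccer arms.** Let d be the soccer-minus-control difference, V_C = p_C(1 − p_C)/n and V_S = p_S(1 − p_S)/n.

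- Pooled SL + SL-V versus CC: noncentrality λ = d² / (V_C + V_S/2), 1 df.
- Planned joint test: when the two effects are equal, the quadratic form reduces to the same λ, but it is referred to 2 df.

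Example, 40% vs 26%, n = 185.14: V_C = 0.24/185.14 = 0.001296; V_S = 0.1924/185.14 = 0.001039; λ = 0.0196 / (0.001296 + 0.000520) = 10.79. The noncentral chi-square gives 84.6% with 2 df and 90.7% with 1 df.

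| CC vs both soccer arms | λ (20% loss) | 2-df | Pooled 1-df | 2-df, 5% loss | Pooled 1-df, 5% loss |
|---|---|---|---|---|---|
| 40% vs 26% | 10.79 | 84.6% | 90.7% | 90.4% | 94.7% |
| 30% vs 17% | 11.15 | 85.8% | 91.6% | 91.3% | 95.3% |
| 30% vs 41% | 6.77 | 64.0% | 73.9% | 72.0% | 80.9% |

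Pooling gains about 6 to 10 points with 20% loss and about 4 to 9 points with 5% loss.

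**6. General statement.** 80% power needs λ = 7.85 with 1 df and 9.63 with 2 df. The ratio is 1.23, so the joint test needs about 23% more information. At λ = 7.85 the 2-df test has 70.9% power.

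**The case against.** The case on the other side is substantial, and most of it stands as a limit on the point.

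- **Month 6 is subordinate.** Both analysis sections say so. The 2-df test keeps its type I error when two arms are alike, so only efficiency is lost.
- **The pairwise contrasts are gated.** They are estimated only if the conditions differ significantly. That limits the risk of misreading but does not remove it: a real soccer effect opens the gate, and SL-V minus SL is then estimated.
- **The contrast may not be exactly null.** A reader might infer that it is null by design. The documents support that for delivered content only. Coaches describe the intervention in detail at invitation, so SL-V men may anticipate the later training, and a late 6-month visit could overlap its start. The contrast also has a use, since it shows whether the arms were alike before they diverged.
- **Harm monitoring.** A reader might infer that the DSMB's 6-month look for iatrogenic effects is underpowered. The article does not support this. It names no test for the DSMB, and nothing stops the board from viewing the soccer arms together.
- **The SAP may add a pooled contrast.** It may. But the article does state a 6-month method, including SL-V minus SL at that visit, and the point concerns that stated method.
- **The power figures are approximate.** They are cross-sectional, whereas the plan models change from baseline in a GLMM and expects smaller standard errors from the longitudinal data. Absolute power may be higher than shown, but the extra degree of freedom still costs power.

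**Conclusion.** The point holds as a modest, inexpensive improvement to a secondary analysis. By the article's own schedule, the nominal 6-month visit compares soccer with control, and the stated analysis does not use that. The cost is about 6 to 10 power points per outcome at the planned 20% loss, and about 4 to 9 points at the pilot's 5% loss. The month-6 SL-V minus SL contrast cannot estimate vocational training, apart from anticipation or late visits.

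The size rests on four assumptions: equal soccer effects in the two arms; the plan's 12- or 24-month employment rates and its drug-use rates carried to month 6; the plan's design effect applied to all arms; and a cross-sectional comparison. The 24-month primary NSO result is unaffected, and the planned 6-month test is not invalid.

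**What to change.** For the secondary 6-month analysis:

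1. Make pooled SL + SL-V versus CC the soccer-effect comparison, with 1 df per outcome. Keep the neighborhood as the randomized unit and keep the planned random effects.
2. Report SL-V minus SL at month 6 only as a labelled check that the arms were alike before vocational training, not as an efficacy contrast.
3. Keep the three-arm contrasts at 12 and 24 months unchanged.
4. Optionally, show the same pooled contrast to the DSMB at 6 months, since the stated concern is men meeting in groups and all 16 soccer neighborhoods bear on it.

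The cost is a change of analysis wording, with no new data and no change to the primary analysis. Trial status says recruitment was still under way at submission, so at that stage the change could still be specified in advance. The one downside is small: pooling averages over any anticipation effect in SL-V. The check in step 2 is where such an effect would appear.

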### Data analysis

Histograms for continuous variables (CES-D, AUDIT-C) will be plotted and screened for outliers and incorrect data and we will build tables for categorical variables, marginally and by treatment condition. Longitudinal data analyses follow the general analysis plan described in detail in Weiss [63]. Longitudinal data will be plotted for continuous variables and empirical summary plots (means ± 2 SE over time, by treatment condition with means and SEs calculated simply at each time point within condition) for all variables.

Neighborhoods and soccer teams are nested within condition; we will use hierarchical regression models with random effects for neighborhood, team within neighborhood, and young men. However, for many outcomes, one or other of the random effects variances will likely be small. Traditional maximum likelihood (ML) software has trouble fitting random effects models when random effect variances are modest or small. However, it is important to include these random effects in the model and to have non-zero variance estimates to properly assess the evidence in the data about the conditions, no matter the size of the variances. Working with SAS or Stata and having to specially adapt models to every outcome due to ML neighborhood and team variance estimated as zero is expensive. The simple but flawed solution of setting the variances to zero causes *p* values comparing conditions to be inappropriately smaller than they merit. In contrast to ML methods, Bayesian methods will not set variance estimates equal to zero, and will properly fit the models we need to our data. We will use the software MCMCglmm [64] or JAGS in R [65], as they both can fit the needed generalized linear mixed models (GLMMs) for discrete and continuous outcomes, estimate all variances appropriately, and run without producing errors, thus saving substantial time and improving the accuracy of the resulting conclusions. To calculate the two degrees of freedom chi-square statistic, we will calculate the posterior mean and covariance matrix of the difference of differences SL-V minus CC, and SL minus CC at 24 months minus baseline and calculate a two degrees of freedom chi square statistic for which we calculate a tail area. The 24-month outcome will be the main time point, with secondary calculations for 6 months minus baseline and 12 months minus baseline.

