### Site

Cape Town is comprised of five major peri-urban settlements with formal and informal housing (shacks). Using charts of field workers of each community and street-intercept surveys of male residents, UCLA matched 24 neighborhoods based on the recency of migration, the density of bars (shebeens), the percentage of informal housing, and water on the premises. Buffer areas of at least 1 km or natural barriers, such as highways, railways, and rivers, separate each neighborhood. Contamination is further prevented by young men’s lifestyles, which lack readily available transport and are concentrated at kiosks, shebeens, and churches in their local areas. In each area, there is formal housing and vast areas of informal shacks. Each neighborhood contains approximately 450–600 households, including roughly 50 young men aged 18–29 years old. We have identified additional neighborhoods as back-up recruitment sites in case a natural disaster or political problem forces exclusion of any triad from our study. Following recruitment, the Data Management Team randomizes triads using R [47], and is not blinded to intervention assignment. Figure 3 summarizes the design of the cluster randomized controlled superiority trial and participant flow.

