### Outcome measures

The primary outcome is the NSO out of 15 outcomes, as explained by Harwood et al. [49]. The 15 specific outcomes are explained below, along with how we intend to analyze each outcome. We analyze each outcome separately. We count the number of outcomes out of 15 where the treatment effect is significant at *p* = 0.05 (two-sided) and that count is the NSO. The single NSO outcome allows us to identify the outcomes affected by the intervention while adjusting for multiple comparisons and the correlations among the outcomes. For fifteen outcomes, the NSO needed for a significant result is either 2 or 3 outcomes, depending on the correlation among the outcomes. As a practical matter, the cutoff is 2 only if the correlation among outcomes is near 0 or near 1. For correlations among outcomes between 0.1 and 0.9 (see Table 2 of Harwood et al. [49]), three significant outcomes give significance at the 0.05 level and, based on similar work with similar variables in these same neighborhoods of Cape Town, we plan to require a minimum of three significant outcomes to declare that the treatment is effective.

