Sample size calculations were carried out in two steps, similar to our previous studies in this area [66], to achieve 80% power with a 0.05 alpha level. First, calculations were carried out to compare two conditions (e.g., SL-V versus SL) on a dichotomous outcome, since dichotomous outcomes generally require larger sample sizes than continuous outcomes. Using employment as an example, we assume an employment rate of 30% at 12 or 24 months in one of the conditions. The sample size will achieve sufficient power if the other condition has 17% (or less) or 41% (or more) employment. We anticipate actual employment differences between groups bigger than 13% (= 30% – 17%) or 11% (= 41% – 30%). We assume 20% loss to follow-up (the pilot had 5% loss at 6 months). This sample size calculation estimates the total sample size for two groups. The additional sample needed for the third group is simply the total sample size divided by two. As a second step, the total sample size is inflated to account for the double nesting of men within teams and teams within neighborhoods. We apply the design effect adjustment (1 + (*n* – 1) × rho) twice, where *n* is the cluster sample size (17 participants per team at the most, and 50 participants per neighborhood) and we take the intraclass correlation (rho) to be 0.01, consistent with previous studies in these neighborhoods [66]. The design effect for our study is the product of these two effects, 1.49 × 1.16 = 1.7284. The CC condition has less design effect than the SL and SL-V conditions, but we have conservatively adjusted the calculations for both design effects across all three conditions; alpha = 0.05, power = 0.8. After carrying out the second step, we arrive at our target sample size of 1200 participants, with 400 per condition. As we will have longitudinal data on employment, our analysis will actually offer smaller standard errors of estimation, and thus we expect to have even greater power than this. In our pilot, 40% of young men had used hard drugs [11]. Comparing two conditions, we have power to detect a decrease to 26% in SL or SL-V from CC. Since for drug use and other analyses we get to adjust for baseline hard drug usage, the power improves substantially.

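### As listed, the neighborhood, team and man random effects drop out of the 24-months-minus-baseline test unless they are allowed to vary over visits, which the plan does not specify

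*Protocol article*

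**What the plan says.** **Random effects.** The Data analysis section states that "we will use hierarchical regression models with random effects for neighborhood, team within neighborhood, and young men". It argues that these variances must be estimated as non-zero, because setting them to zero would make the p values comparing conditions too small. This is its main reason for choosing Bayesian software.

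**Fixed effects.** For binary outcomes measured at all four visits, the Missing data section says "we expect to treat time categorically, and model main effects for condition, time, and time by condition interaction".

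**Tested quantity.** The Data analysis section uses a 2-df chi-square on SL-V minus CC and SL minus CC, each taken as 24 months minus baseline. The result feeds the primary endpoint: "We count the number of outcomes out of 15 where the treatment effect is significant at" the two-sided 0.05 level, with at least three such outcomes required.

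**Randomization.** Neighborhoods were matched, and the Site section says "Following recruitment, the Data Management Team randomizes triads using R".

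**Sample size.** This text, also under Missing data, applies a design effect of 1.7284 for teams and neighborhoods.

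No neighborhood-by-time, team-by-time or triad term is named anywhere.

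**The concern.** A neighborhood effect that is the same at every visit enters both the 24-month and the baseline value, so it subtracts out of the change. The same holds for a constant team or man effect. The standard error of the tested contrast then rests on the number of men. It does not reflect how differently neighborhoods move over 24 months, although neighborhoods are the units randomized. The protection that the Data analysis section expects from non-zero cluster variances is not delivered for the contrast that the same section tests.

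The team term has a further problem. Under Condition 2, coaches invite men only once all baseline assessments in the neighborhood are done, and controls have no teams. A team effect produced by the intervention therefore lies wholly in the change, and a constant term puts it in the wrong place.

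At stake is the 5% level of each component test. The three-outcome cutoff presumes that level.

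**Working it through.** **1. The plan's own design effect.** (1 + 49 × 0.01) × (1 + 16 × 0.01) = 1.49 × 1.16 = 1.7284, which reproduces. It applies to a comparison of two proportions at one follow-up visit.

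**2. Cancellation.** Write the linear predictor for man *i* in team *j* of neighborhood *k* at visit *t* as fixed(condition, *t*) + N_k + T_jk + M_i. The value at 24 months minus the value at baseline is fixed(condition, 24) − fixed(condition, 0). N, T and M are gone. This is exact on the linear predictor. It is approximate for estimates under a logit link or with missing visits. A simulation on a continuous scale (24 neighborhoods, 40 men, 4 visits, 3,000 runs) agrees: with perfectly stable neighborhood effects, size was 0.049 at an intraclass correlation of 0.01 and 0.048 at 0.05. The neighborhood variance has no influence on the test.

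**3. Size when neighborhood effects drift.** Inputs:
- ρ = 0.01, from the sample size text.
- m = 40 men per neighborhood: 50 less 20% ("We assume 20% loss to follow-up").
- w = within-man correlation, assumed 0.3 to 0.5.
- c = correlation of a neighborhood's effect between baseline and 24 months. It is not in the article and is varied here.

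Ratio of true variance to modelled variance of the contrast:

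V = 1 + mρ(1 − c) / [(1 − ρ)(1 − w)]

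True size of the nominal 5% 2-df test = 0.05^(1/V).

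| c | V (w = 0.3) | size | V (w = 0.5) | size |
|---|---|---|---|---|
| 1 | 1.000 | 5.0% | 1.000 | 5.0% |
| 0.8 | 1.115 | 6.8% | 1.162 | 7.6% |
| 0.5 | 1.289 | 9.8% | 1.404 | 11.8% |

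Example: c = 0.5, w = 0.5 gives V = 1 + (40 × 0.01 × 0.5)/(0.99 × 0.5) = 1.404, and 0.05^(1/1.404) = 0.118.

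The continuous-scale simulation at w = 0.5 gave 8.3% (c = 0.8) and 11.4% (c = 0.5). A separate simulation with binary outcomes (6,000 trials per setting, intraclass correlation 0.01 on the latent scale) gave 5.0%, 6.3% and 8.0% at c = 1, 0.8 and 0.5. In the continuous-scale runs at ρ = 0.01, an analysis of variance on the 24 neighborhood mean changes held 4.4% to 5.1%.

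**4. Team effect.** Assume a team intraclass correlation of 0.01 (the plan's value), three teams per neighborhood, and team effects present only at 24 months in SL and SL-V. Size is then about 6% even with stable neighborhood effects, and about 8-9% at c = 0.8.

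**5. Effect on the primary count.** PEth is measured at 24 months only, so the cancellation concerns 14 outcomes. Treat the outcomes as independent, with 14 tests at size *a* and PEth at 5%. Then P(three or more) = 0.95 × P(Bin(14, a) ≥ 3) + 0.05 × P(Bin(14, a) ≥ 2). This is 3.6% at a = 5%, 7.5-9.5% at a = 6.8-7.6%, and 16-24% at a = 9.8-11.8%. It is an illustration only, because the protocol describes correlated outcomes.

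**6. Triads.** With c = 0.5, w = 0.5 and half of the neighborhood drift shared within triads, the neighborhood-level test that ignores triads has size 3.1%, and the random-intercept test falls from 11.4% to 7.4%. Leaving triads out therefore lowers the rejection rate.

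The gain from blocking depends on the share of the contrast variance that lies between neighborhoods: s = ρ(1 − c) / [ρ(1 − c) + (1 − ρ)(1 − w)/m]. This is 0 at c = 1 and 10-14% at c = 0.8. If triads explain 30-70% of it (assumed), the gain 1/(1 − 0.3s) − 1 to 1/(1 − 0.7s) − 1 is 0% at c = 1 and about 3-11% at c = 0.8.

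**The case against.** **The article does not say intercepts only.** It lists the levels that receive random effects and defers longitudinal modelling to a cited general plan that is not shown. If that plan has cluster effects varying by visit, the problem disappears. This stands, and it is why the point is conditional. However, the article names the random effects, speaks of one variance per level, and names the fixed terms and the contrast. As written, these do not deliver the protection it claims for them.

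**The team term may already be restricted.** Nothing says it applies at baseline or to controls, and the sample size text recognizes a smaller design effect in CC. That also stands, and one sentence would settle it.

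**The inflation rests on an unstated figure.** This is correct. With fully stable neighborhood effects the neighborhood part causes no error, and the binary simulation shows less inflation than the formula.

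**Stronger readings that the document does not support:**
- A reader might infer that leaving out triads is a further way of ignoring clustering. It works in the opposite direction: it is conservative and costs power.
- A reader might compute the gain from triads at a single visit, where the between-neighborhood share is 0.01/(0.01 + 0.99/40) = 29%, and obtain 9-25%. That share does not carry over to the change contrast, where stable triad effects also cancel.
- A reader might say that the analysis contradicts the 1.7284 design effect. That factor was used, conservatively, for a single-visit comparison. Planning with more variance than the analysis uses is not a contradiction.
- A reader might extend the point to all 15 outcomes. PEth has no baseline value and is not affected.

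**Conclusion.** The concern holds conditionally. Read naturally, the stated model removes neighborhood and team variation from the main contrast for 14 of the 15 outcomes, against the purpose that the Data analysis section gives for those terms. True size of each nominal 5% test is 5% if neighborhood effects are stable, about 7-8% at a between-visit correlation of 0.8 (6.3% in the binary simulation) and about 10-12% at 0.5 (8.0% in that simulation). These neighborhood figures use the plan's intraclass correlation of 0.01 and 40 men followed per neighborhood. They also rest on an assumed within-man correlation of 0.3-0.5 and on between-visit correlations for which the article has no figure. A team effect arising after baseline would add to them. The absence of triads is a matter of efficiency, not validity.

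**What to change.** State in the analysis model:
1. a neighborhood-by-time random effect;
2. a team random effect that acts only at visits after baseline and only in SL and SL-V;
3. as a check, a test based on the 24 neighborhood-level changes.

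If the full plan already contains the first two, saying so is enough. The cost is wording and somewhat wider intervals. No new data are needed, and recruitment was still under way when the article was submitted.

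Separately, for efficiency, include the eight randomized triads as a blocking factor interacting with time, since a time-constant triad term would cancel like the others. This spends 7 degrees of freedom in the neighborhood-level comparison. Any gain quoted for it should refer to the change contrast, where it is zero if neighborhood effects are stable.
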